## Abstract

**Abstract:**

**Introduction:**

The Dutch guideline ‘Gallstone disease’ (2016) recommends performing a cholecystectomy within 72 hours following endoscopic retrograde cholangiopancreatography (ERCP) for common bile duct stones to prevent recurrent gallstone-related complications. Nevertheless, guideline adherence in the Netherlands remains low, and the time between ERCP and cholecystectomy often exceeds 72 hours. Our project aims to improve national guideline adherence to 85% or higher and thereby reduce the incidence of gallstone-related complications after ERCP.

**Methods and analysis:**

The Dutch-TIMELINESS is a multicentre implementation project using a Multiphase Optimisation Strategy. The project includes 61 Dutch hospitals. In phase 1, all patients undergoing ERCP for choledocholithiasis from 1 January to 31 March 2023 will be analysed to serve as a benchmark. In phase 2, each hospital develops and implements its own tailored protocol in line with the guideline, guided by the benchmark data. In phase 3, from 1 December 2025 to 31 March 2026, the new protocols will be prospectively evaluated with real-time monitoring and refined as necessary. Statistical methods are predefined in the protocol.

**Ethics and dissemination:**

The Medical Research Ethics Committees United reviewed the protocol and concluded it does not fall under the scope of the Medical Research Involving Human Subjects Act (WMO). Local institutional research departments and the board of directors reviewed and approved the protocol in all participating hospitals. Results will be published in international peer-reviewed scientific journals and presented at national conferences.

## Introduction and rationale

 Yearly, 30 000 patients are diagnosed with cholecystolithiasis in the Netherlands.^1
2^ These gallstones may migrate into the common bile duct (CBD) which is known as choledocholithiasis.^3^ The Dutch guidelines recommend treating symptomatic choledocholithiasis with papillotomy and stone extraction through endoscopic retrograde cholangiopancreatography (ERCP), followed by laparoscopic cholecystectomy within 72 hours.^4^ Despite this recommendation, adherence in clinical practice remains limited.

The evidence for routine cholecystectomy following ERCP for choledocholithiasis is extensive. In 2002, a randomised controlled trial (RCT) demonstrated that cholecystectomy following ERCP reduced the risk of recurrent gallstone complications from 47% to 2% compared with a wait-and-see approach.^5^ These findings have been replicated in other RCTs.^6–8^ Subsequent meta-analysis even showed a reduced risk of mortality for routine cholecystectomy compared with wait-and-see.^9^

Despite this strategy, approximately 20% of patients develop recurrent symptoms or complications while awaiting elective cholecystectomy. This can be prevented by early cholecystectomy, within 72 hours after ERCP.^10–14^ This timeframe avoids 10% redo ERCPs due to recurrent CBD stones in the waiting time and 14% emergency cholecystectomies due to cholecystitis.^14^ An early cholecystectomy following ERCP is also the most effective strategy in terms of costs, and therefore a significant argument in this time of increasing healthcare expenses.^15^

Performing CBD clearance and cholecystectomy as a single-session procedure instead of a two-step procedure is even more effective.^16–18^ This virtually eliminates the chance for recurrent biliary events and shortens hospital stay. However, the single-session procedure is logistically challenging in the Dutch healthcare system: the success rate of endoscopic removal of CBD stones is high, and subsequently, the experience with laparoscopic CBD exploration has ceased. For a single-session treatment, thus two specialists are required (gastroenterologist and surgeon), posing big logistical challenges. Therefore, in the Netherlands, the two-step procedure is standard.

The 72-hour timeframe for the two-step procedure has been recommended by the Dutch guidelines since 2016, but compliance remains low. Based on a short survey with 40 gastroenterologists from 40 hospitals in January 2024, it was estimated that only 10% of patients undergoing ERCP for choledocholithiasis receive a cholecystectomy within 72 hours. The underlying reasons for this low percentage may include the absence of standardised protocols, logistical challenges, unclear ownership of care, a lack of benchmark data and inadequate performance feedback.

To address the causes of poor guideline adherence and to improve compliance, the Dutch-TIMELINESS project was designed as a 2-year implementation project using a Multiphase Optimisation Strategy (MOST).^19^ The Dutch-TIMELINESS project aims to achieve that in 2 years’ time, 85% of patients receive a cholecystectomy within 72 hours following successful ERCP in the Netherlands. Hereby, we aim to reduce complications, re-interventions, emergency surgeries and associated healthcare costs.

## Methods

### Primary objective

To achieve adherence rates of over 85% for cholecystectomy within 72 hours following successful ERCP for choledocholithiasis in the Netherlands.

This goal of 85% is in line with the results of a similar project in the UK, set up to improve timely emergency cholecystectomy rates for cholecystitis. This project demonstrated that significant improvement is feasible within a 2-year timeframe. Through a quality improvement collaborative, the rate of performing emergency cholecystectomies within 7 days increased from 5% to 85% in 2 years.^20^

### Project design

This project is reported in accordance with the StaRI guidelines for implementation studies.^21^ The Dutch-TIMELINESS is a national before-after implementation project comprising 61 hospitals performing ERCP in the Netherlands. This implementation project is designed using the Updated Consolidated Framework of Implementation Research (CFIR) and the strategies mentioned in the strategy tool from The Netherlands Organisation for Health Research and Development. These strategies are based on the CFIR-ERIC matching tool.^22
23^ The CFIR is a listing of constructs with potential influencing factors for implementation, developed by Damschroder *et al.* in 2009.^24^ By using the CFIR, barriers and facilitators of the implementation process will be identified. During the conduction of the Dutch-TIMELINESS, the implementation process will be evaluated and readjusted at predefined time points, if needed.

### Description

The MOST is adopted as implementation strategy.^19^ This strategy consists of three subsequent phases: preparation, optimisation and evaluation. The Dutch-TIMELINESS project will be organised in three phases across 24 months, accordingly.

#### Phase 1: baseline measurement, determining barriers and providing performance feedback

The objective of the first phase is to provide centre-specific performance feedback to all participating hospitals, based on their local baseline measurement. Furthermore, this phase enables us to identify best practices, additional local barriers and local opportunities. The Dutch-TIMELINESS project will retrospectively analyse all patients that underwent ERCP for choledocholithiasis in the period between 1 January 2023 and 31 March 2023. Data regarding patient, treatment and outcome characteristics will be extracted from the patient’s electronic health record. Frailty will be measured using the validated modified Frailty Index-5 (mFI-5).^25^ We decided on using this frailty index as it was proven a strong predictor of mortality and postoperative complications in geriatric patients undergoing cholecystectomy.^26^

The data collection in phase 1 will be executed conform the Snapshot method.^27^ The Dutch Snapshot Research Group (DSRG) is a Dutch surgical network that facilitates research collaboration in the Netherlands, initiated in 2014. The Snapshot research method is collaborative research with the aim of easily collecting data from multiple hospitals, with help from residents in each centre. For that reason, the approval of the DSRG was obtained prior to the start of the Dutch-TIMELINESS. For this first phase, data has been collected since February 2025. The timing of data completion differed across participating centres, with some centres completing their registrations earlier than others.

#### Phase 2: engaging local stakeholders and establishing tailored guidelines

The objective of this second phase is to establish a tailored protocol for the treatment of choledocholithiasis in each participating hospital. First, the participating hospitals will receive performance feedback based on their baseline measurement. This feedback will contain the local percentage of guideline adherence compared with the average results and best practices. The hospitals that perform best will be asked to share their protocols and policies around choledocholithiasis. The summary provided to each hospital will also include their own essential data needed for logistics, such as the mean number of patients per week, the number of referred patients, the success rate of the ERCP and the time between diagnosis and ERCP. The latter may be key, as proper planning and teamwork between gastroenterologist and surgeon from diagnosis onwards will buy valuable time. Second, guided by the summarised data, local barriers and determinants of success will be found. Each hospital will gather their local stakeholders. These stakeholders will at least consist of the gastrointestinal surgeons, gastroenterologists and anaesthesiologists. Together, they will establish a local, tailored guideline. All parties involved will be informed by the local investigators and will be actively included in the process.

#### Phase 3: evaluation and adjustments

The objective of this third phase is to evaluate the adherence to the newly established guideline. The aim is to increase the percentage of patients undergoing cholecystectomy within 72 hours after ERCP to at least 85%. During this phase, local investigators will prospectively include patients undergoing ERCP in the period from 1 December 2025 to 31 March 2026. Data regarding patient, treatment and outcome characteristics will be extracted from the patient’s health record. Every 4 weeks, the use of the newly established local guideline will be evaluated and, if necessary, adjusted by a designated gastroenterologist and surgeon.

To visualise a detailed description of the implementation process, we developed a logic model^28^ (figure 1) and a timeline with events (figure 2).

**Figure 1 F1:**
[figure not shown]
Logic model of the TIMELINESS project. The model displays the inputs, outputs and short- and long-term outcomes across three phases. ERCP, endoscopic retrograde cholangiopancreatography; ZonMW: the Dutch organisation for knowledge and innovation in health, healthcare and well-being.

**Figure 2 F2:**
[figure not shown]
Timeline with events. The timeline illustrates the three phases of the TIMELINESS project and lists key activities for each phase.

#### Information campaign

An information campaign will be held throughout the duration of the project, as briefly outlined in the logic model and the timeline (figures 1 and 2). A series of webinars will be organised to inform and engage participants during phases 1, 2 and 3. Information will be disseminated through presentations at local and national conferences. The project’s aim and protocol will be published in a variety of professional magazines and newsletters targeting the key stakeholders, including surgeons, gastroenterologists, anaesthesiologists, endoscopy nurses and operating room nurses. Additionally, the treatment strategy (cholecystectomy within 72 hours following ERCP) will be incorporated in the biannual course on biliary disease for surgical residents. Finally, the treatment strategy will be highlighted in information leaflets for patients with gallstone disease, provided by the Dutch Digestive Health Fund. During the entire process, updates and information will be spread via social media platform LinkedIn and via email to keep the whole network engaged.

### Targeted sites, population and eligibility criteria

In the Netherlands, 62 hospitals perform ERCPs. This project comprises a total of 61 hospitals, including 60 hospitals that perform ERCPs. One hospital that does perform ERCP is not involved, as they are not performing ERCP for choledocholithiasis. One regional hospital that does not perform ERCPs but has a tight collaboration with a hospital in Belgium that performs ERCPs for their patients has been included. Since they had a strong incentive to optimise their care for these patients, they were included in the project. This makes a total of 61 hospitals included in the project. Six of the 61 hospitals are academic hospitals and part of the Netherlands Federation of University Medical Centres. 28 of the remaining 55 hospitals are part of the Association of Tertiary Medical Teaching Hospitals. 26 hospitals are regional hospitals. Finally, one of the participating hospitals is a specialised cancer institute that also performs ERCP for choledocholithiasis and was therefore considered eligible for inclusion.

For the first phase, all patients aged 18 years or older who underwent ERCP for choledocholithiasis in the period between 1 January 2023 and 31 March 2023, with a gallbladder in situ, will be included. This period was selected because it was thought to accurately represent the best everyday practices. COVID-19 was no longer active, and there were no significant holidays that might have interrupted operation schedules. Moreover, the Dutch-TIMELINESS could not have influenced results, since the project was not yet pitched or designed. Patients included in this period will be followed for 2 years after the baseline ERCP. This extended follow-up will be used for secondary and descriptive analysis of recurrent biliary problems. The primary before-after comparison will focus on guideline adherence within 72 hours after successful ERCP.

In phase 2, no patient data will be collected.

In phase 3, all patients 18 years or older diagnosed with choledocholithiasis, with a gallbladder in situ, who will undergo ERCP in the period between 1 December 2025 and 31 March 2026, will be included. This period was chosen to match the calendar quarter used in phase 1. December will be used as a wash-in period to separate the start-up effects from the true effect of the implementation. Data from this period will be excluded from the analysis to minimise bias from partial adoption of the local protocol. The follow-up period for phase 3 will be 8 weeks from the date of ERCP, to ensure more complete data on elective cholecystectomies and postoperative complications. A prolonged follow-up is not required as the primary aim of this phase is to evaluate the implementation process rather than long-term outcomes.

For the primary analysis, the population will be defined identically in both phases. All eligible patients with a gallbladder in situ who underwent a first successful ERCP for choledocholithiasis within the predefined inclusion window. Patients who are not candidates for cholecystectomy due to surgical contraindications will be excluded from the analysis. These surgical contraindications include absolute contraindications for general anaesthesia (such as haemodynamic instability or extensive comorbidities) as determined by the attending anaesthesiologist, liver cirrhosis, loco-regional malignancy, gallbladder fistula and extensive or complicated previous abdominal surgery. These patients will be recorded in the database but excluded from outcome analysis. Patients who decline cholecystectomy or are advised against cholecystectomy for non-surgical reasons will remain included. Patients who are transferred will be registered in the hospital where the successful ERCP was performed. Patients who are transferred solely for cholecystectomy will also be registered under the ERCP hospital. This approach ensures that the primary endpoint is evaluated in comparable populations in both periods.

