During the process of project design, several questions of scientific interest were encountered that will be addressed, using the data generated by the Dutch-TIMELINESS project. These predefined secondary objectives, along with a brief plan for their analysis, are presented in online supplemental file 1. These secondary objectives include:

To determine the effect of the time between diagnosis of choledocholithiasis and ERCP on morbidity, the success rate of the first ERCP, complications during ERCP and post-ERCP.To determine the effect of the time between ERCP and cholecystectomy on morbidity and surgical complications.To determine whether frailty modifies the association between cholecystectomy within or after 72 hours and morbidity in frail patients.To determine whether gallstones on preoperative imaging are associated with recurrent biliary events before cholecystectomy and with the presence of intraoperative gallbladder stones.To compare national hospital-level healthcare costs before and after the Dutch-TIMELINESS project.To evaluate the adoption, implementation and maintenance of the Dutch guidelines following the Dutch-TIMELINESS project.

Strengths and limitations of this studyNational coverage: participation of all centres in the Netherlands performing endoscopic retrograde cholangiopancreatography for choledocholithiasis.The phased implementation strategy benchmarks current practice, customises protocols and evaluates results to enable local changes while following national guidelines.Before-after design: system changes over time might influence adherence independent of the intervention.Selection bias: non-participation in the prospective phase might lead to potential selection.Information bias: in the retrospective phase, loss to follow-up might occur.

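### Phase 3 follow-up is counted from ERCP, so observation after cholecystectomy shrinks with delay, and phase 3 surgical complications are under-counted for surgery after about day 26 (for an assumed 30-day window)

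*Protocol article*

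**What the plan says.** All references are to the protocol article.

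- **Phase 3 window** (Targeted sites, population and eligibility criteria): follow-up "will be 8 weeks from the date of ERCP, to ensure more complete data on elective cholecystectomies and postoperative complications". The section adds: "A prolonged follow-up is not required as the primary aim of this phase is to evaluate the implementation process rather than long-term outcomes". No follow-up counted from the date of surgery is given.
- **Phase 1 window** (same section): "Patients included in this period will be followed for 2 years after the baseline ERCP", and "This extended follow-up will be used for secondary and descriptive analysis of recurrent biliary problems".
- **Objective affected** (secondary objectives, listed under Primary objectives' statistical plan): "To determine the effect of the time between ERCP and cholecystectomy on morbidity and surgical complications". The secondary objectives are to be addressed "using the data generated by the Dutch-TIMELINESS project". The article does not say whether that means phase 1, phase 3 or both, and it places the analysis plan in online supplemental file 1, which was not available for this review.

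**The concern.** The exposure in this objective is the time from ERCP to surgery. In phase 3 the time available to record a surgical complication is 56 days minus that same exposure, so the completeness of the outcome depends on the exposure by construction. Elective operations, which come later, are the ones cut short, although the 8 weeks are justified by the completeness of data on exactly those operations. If phase 3 data are used as collected, some complications of later surgery are never recorded, and the comparison leans against the early-surgery policy that the project is implementing. An analysis plan cannot restore observations that were not collected.

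**Working it through.** **Inputs from the article.** Phase 3 follow-up is 8 weeks = 56 days from ERCP; phase 1 follow-up is 2 years, taken as 730 days. The Sample size section gives 61 hospitals, 35 patients per hospital per period and 10% non-inclusion. Adherence is about 10% before (Introduction and rationale) and 85% expected afterwards (Sample size).

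**Assumptions, not in the article.** A 30-day complication window; the timing of complications after surgery; late operations spread evenly over days 4 to 84; a true complication rate of 10%.

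**1. The plan's own figure.** 2 × 61 × 35 × 0.90 = 3843, as stated, or 1921.5 per period. The article gives no figure for observation time after surgery.

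**2. Observation after surgery in phase 3.** For surgery on day d it is 56 − d days. A full 30 days requires d ≤ 56 − 30 = 26.

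**3. Share of 30-day complications captured.** With exponential onset of mean m days, capture = (1 − exp(−min(30, 56 − d)/m)) / (1 − exp(−30/m)). With onset spread evenly over 30 days, capture = min(30, 56 − d)/30.

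| Day of surgery | Days observed | m = 3 | m = 7 | m = 14 | Even |
|---|---|---|---|---|---|
| 3 | 53 | 100% | 100% | 100% | 100% |
| 26 | 30 | 100% | 100% | 100% | 100% |
| 35 | 21 | 100% | 96% | 88% | 70% |
| 42 | 14 | 99% | 88% | 72% | 47% |
| 49 | 7 | 90% | 64% | 45% | 23% |

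The loss depends strongly on timing: with very early onset (m = 3) it is small until about day 49. Its direction within phase 3 does not change.

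**4. Average over late operations in phase 3.** Days 4 to 84 are 81 days.
- Fully observed (days 4–26): 23/81 = 28%.
- Partly observed (days 27–56): 30/81 = 37%.
- Outside follow-up (days 57–84): 28/81 = 35%.

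Mean capture over days 27–56 is 0.764 for m = 7 and 14.5/30 = 0.483 for even onset. Among the operations seen, capture is (23 + 30 × 0.764)/53 = 0.87 and (23 + 14.5)/53 = 0.71. A true 10% would read as 8.7% or 7.1% in late surgery, against 10% in early surgery.

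**5. Number of events.** At 85% adherence at most 0.15 × 1921.5 = 288 phase 3 patients have late surgery. Then 288 × 53/81 = 188 operations are seen, with about 19 complications at 10%, of which about 2.5 (13%) to 5.5 (29%) are missed. If adherence stayed at 10%, the late group would be 0.90 × 1921.5 = 1729, with 1729 × 53/81 = 1131 operations seen, about 113 complications and about 15 to 33 missed.

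**6. Pooling the phases.** Assume that everyone not operated on within 72 hours has later surgery.
- Phase 1: 192 early and 1729 late. Phase 3: 1633 early and 288 late.
- Late patients from phase 1: 1729/(1729 + 288) = 86%. Early patients from phase 3: 1633/(192 + 1633) = 89%.
- Mean observation after early surgery (day 2): (192 × 728 + 1633 × 54)/1825 = about 125 days.
- Mean observation after late surgery: at day 28, (1729 × 702 + 288 × 28)/2017 = about 606 days; at day 90, (1729 × 640 + 0)/2017 = about 549 days.

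Without a common window, late surgery is therefore observed far longer than early surgery, and the distortion favours early surgery.

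**The case against.** The strongest reply is that the harm depends on an analysis plan that is not shown. Online supplemental file 1 may use phase 1 only, where 2 years of follow-up leaves essentially no truncation, or it may define a fixed complication window. That stands as a limit on the claim. It does not remove the point, because under the stated follow-up no phase 3 operation after day 26 can have 30 observed days, whatever the supplement says.

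The effect may also be small. If the phases are pooled with a common 30-day window and adherence reaches 85%, there are about 1729 + 188 = 1917 late operations seen and about 192 complications. Losing 2.5 to 5.5 of them moves 10% to about 9.9% or 9.7%. That also stands, although a phase 3-only comparison, or adherence well below target, would lose more.

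The article promises only more complete data, and says that long-term outcomes are not the aim of phase 3. The first remark is fair. The second does not answer the point, since a short window after surgery is not a long-term outcome, and postoperative complications are part of the article's own reason for the 8 weeks.

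Finally, operations after day 56 drop out of both numerator and denominator, so on their own they do not lower a complication rate. This is correct. The under-count in the rate comes from operations on days 27 to 56.

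**Conclusion.** The point holds for any use of phase 3 data on surgical complications by interval. Observation after surgery falls by one day for each day of delay, and that needs no assumption. With a 30-day window the under-count begins after day 26 and, within phase 3, favours delay. The capture of 71% to 87% among late operations seen rests on the assumed window, spread of surgery dates and onset times, and is an illustration rather than a forecast.

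A reader might infer three stronger things that the document does not support:

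- *That the objective as a whole is biased in favour of delay.* The article does not tie it to phase 3, and pooling without a common window would reverse the direction.
- *That all surgery beyond 72 hours is under-counted.* Surgery on days 4 to 26 has a full 30 days.
- *That the frailty objective shares the fault.* Its outcome is morbidity; if that is counted from ERCP, every phase 3 patient has the same 8 weeks.

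The primary outcome, cholecystectomy within 72 hours, is unaffected. The change should be made because it is cheap and removes unequal ascertainment in a named secondary objective.

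**What to change.** State that surgical complications are counted over one fixed window from the date of cholecystectomy, for example 30 days, in both phases. In phase 3, extend record review to the end of that window for every patient operated on within the 8 weeks, and keep 8 weeks from ERCP for the other outcomes. State also which phase or phases supply the data for this objective.

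If the 8-week limit must stay, either restrict the phase 3 surgical-complication analysis to operations whose whole window lies inside it (up to day 26 for 30 days), or use phase 1 only.

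Cost: a short change of text and later chart closing for operations on days 27 to 56, at the latest day 56 + 30 = 86 after ERCP. These patients are a subset of the at most about 288 late phase 3 patients at 85% adherence, and the data come from routine records. The restriction needs no extra data collection but leaves fewer late cases.

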### Primary objectives’ statistical plan

To determine whether this implementation project has improved guideline adherence, we will perform a before-and-after analysis as previously described in the methods section. The primary outcome measure is adherence to the Dutch National Guideline ‘Gallstone disease’,^4^ defined as the proportion of patients undergoing cholecystectomy within 72 hours after successful ERCP. These percentages will be reported per hospital (anonymously) and as national mean. The results will be depicted using a slope chart showing the change in guideline adherence per hospital between the two time points we will compare: January to March 2023 versus January to March 2026. The proportion of hospitals reaching the predefined 85% adherence target will also be reported.

Due to the non-randomised nature of this project, we expect differences in baseline characteristics between hospitals and time periods. The primary statistical analysis will use a mixed-effects logistic regression model fitted at patient level. Period defined as year 2023 versus 2026 will be included as the fixed effect of primary interest. To adjust for case-mix, prespecified variables will be included as fixed effects. These include: age, body mass index, American Society of Anaesthesiologists classification, history of biliary disease, history of abdominal surgery, use of anticoagulation, use of immunosuppressants, mFI-5 score and dementia. A random intercept per hospital will account for clustering. To improve clinical interpretability, marginal model-based adjusted adherence rates for each period and the adjusted absolute difference in adherence between periods will also be derived from the mixed-effects model and reported with 95% CIs.

Missing data will be handled using multiple imputation under the assumption of missing-at-random. The imputation model will include the outcome, period, hospital, all variables included in the analysis model. The number of imputations will be at least 20. Estimates will be pooled according to Rubin’s rules. Prespecified sensitivity analysis will include: a complete case analysis, an unadjusted mixed-effects model including period as the only fixed effect, a hospital-level paired analysis in which the change in adherence is calculated for each hospital and summarised nationally.

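### The exclusion for surgical contraindications has no assessment time, so patients who have already missed the 72-hour endpoint can leave the denominator and reported adherence can be pushed upward

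*Protocol article*

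**What the plan says.** The endpoint is adherence, "defined as the proportion of patients undergoing cholecystectomy within 72 hours after successful ERCP" (Primary objectives’ statistical plan). Each patient's result is therefore known at 72 hours.

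The analysis population is set out under Targeted sites, population and eligibility criteria. There the plan states: "Patients who are not candidates for cholecystectomy due to surgical contraindications will be excluded from the analysis". The listed grounds include "absolute contraindications for general anaesthesia (such as haemodynamic instability or extensive comorbidities) as determined by the attending anaesthesiologist". They also include liver cirrhosis, loco-regional malignancy, gallbladder fistula, and extensive or complicated earlier abdominal surgery. On handling, the plan says: "These patients will be recorded in the database but excluded from outcome analysis". By contrast, "Patients who decline cholecystectomy or are advised against cholecystectomy for non-surgical reasons will remain included".

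No date or event is given at which candidacy is to be assessed. The same section states that the population is defined identically in the two phases and concludes that the populations are comparable.

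The three prespecified sensitivity analyses are a complete-case analysis, an unadjusted mixed model and a hospital-level paired analysis. None of them returns the excluded patients to the denominator.

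**The concern.** Membership of the denominator should not depend on anything that happens after the endpoint is settled. Cirrhosis and earlier abdominal surgery normally pre-date the ERCP. Haemodynamic instability, a malignancy, a fistula or an anaesthesiologist's finding of unfitness may come later. For a patient waiting for elective surgery, the anaesthetic assessment itself may fall after 72 hours.

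A patient operated on within 72 hours was evidently a candidate. A patient not operated on by then, who afterwards becomes a non-candidate, can be dropped under the rule as written instead of counting as non-adherent. Identical and perfect recording in 2023 and 2026 would not cure this, and neither would a larger sample.

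It can happen in practice. Phase 1 is abstracted retrospectively, with data collected since February 2025 for ERCPs done in early 2023, so the later course is visible to the person completing the form.

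At stake are the national adherence level, which the Sample size section treats as the main quantity to be estimated around the target, and the proportion of hospitals reaching 85%.

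**Working it through.** **Inputs from the Sample size section.** Baseline adherence is about 10% and the target is 85%. The plan expects 35 patients per hospital and 2135 per period, with 10% non-inclusion and a design effect of 4.40.

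**The plan's own precision.** N per period = 0.9 × 2135 = 1921.5. Half-width = 1.96 × √(0.85 × 0.15 × 4.40 / 1921.5) = 0.0335, or 3.35 percentage points. The stated ±3.4 reproduces. It describes sampling error only and does not cover the effect examined here.

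**Effect of the open-ended rule.** Let p be adherence when status is fixed before the outcome is known. Let f be the share of non-adherent patients removed for a contraindication that arises after 72 hours. The numerator is unchanged and the denominator shrinks by f(1 − p), so

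observed adherence = p / (1 − f(1 − p)),

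which exceeds p for every f > 0 and p strictly between 0 and 1. The documents do not give f, so it is an assumption.

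| p | f = 5% | f = 10% | f = 20% |
|---|---|---|---|
| 10% | 10.5% | 11.0% | 12.2% |
| 83% | 83.7% | 84.4% | 85.9% |
| 85% | 85.6% | 86.3% | 87.6% |

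For example, 0.85 / (1 − 0.05 × 0.15) = 0.85 / 0.9925 = 85.6%.

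**Removal needed to cross the target.** The share of all patients that must leave is 1 − p/0.85.
- For p = 83% this is 2.4%, about 45 of 1921 patients, or f = 0.0235 / 0.17 ≈ 14%.
- For p = 84% it is 1.2%, or f ≈ 7%.

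**Single hospital.** With 35 patients, 29/35 = 82.9% misses the target. Removing one non-adherent patient gives 29/34 = 85.3%, which meets it.

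**Before-after contrast.** Removal multiplies the crude odds in a period by 1/(1 − f), so the crude odds ratio is multiplied by (1 − f in phase 1)/(1 − f in phase 3). Take 10% versus 80% as an illustration, with a difference of 70.0 points and an odds ratio of 36.0:

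| f, phase 1 | f, phase 3 | Difference (points) | Odds ratio |
|---|---|---|---|
| 10% | 10% | 70.6 | 36.0 |
| 10% | 5% | 69.8 | 34.1 |
| 5% | 10% | 71.2 | 38.0 |

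The contrast can move either way.

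**The case against.** The strongest defence is that the ordinary reading is status at presentation. The rule stands among the eligibility criteria, in the present tense, beside the gallbladder-in-situ and first-successful-ERCP conditions. Most listed items usually pre-date the ERCP, and nothing says that a later event undoes eligibility. The timing might also be fixed in case report form definitions that are not shown. This makes the likely effect smaller, but it does not close the gap. Anaesthetic fitness is tied to a clinician's judgement with no date. The article sets out the population rules in detail, and under General it says that it presents the complete protocol.

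A reader might also infer more than the documents support:

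- **That the before-after difference is biased upward.** This is not shown. Equal f leaves the crude odds ratio unchanged, and more removal in 2023 lowers the contrast.
- **That contraindications are searched for over 2 years in phase 1 and 8 weeks in phase 3.** The follow-up lengths are stated ("Patients included in this period will be followed for 2 years after the baseline ERCP" and "The follow-up period for phase 3 will be 8 weeks from the date of ERCP"). However, the plan assigns the long follow-up to secondary and descriptive analyses, and the 8 weeks to elective operations and postoperative complications. An unequal search window is an inference.
- **That the inflation is large.** Removing 3% or 5% of all patients at 85% adherence would give 87.6% or 89.5%. That means 20% or 33% of non-adherent patients (0.03/0.15 and 0.05/0.15) acquiring a late contraindication, which nothing in the documents suggests.
- **That the rule can never remove an adherent patient.** This holds for contraindications arising after 72 hours. A malignancy or fistula found at a timely operation could remove an adherent patient if the list were applied literally, although the wording about candidates makes that reading unlikely.

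**Conclusion.** The concern holds in a limited form. The rule fixes no assessment time, and patients who have already failed the endpoint can be dropped under it. The resulting error in each period's adherence level, and in the share of hospitals reaching 85%, runs in one direction: upward. Its effect on the before-after contrast has no known sign.

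The size is unknown and probably small. Under the assumed f of 5% to 10%, the inflation is 0.6 to 1.3 points at a true 85% and 0.5 to 1.0 points at a true 10%. Nationally it would change the reading against the target only when true adherence lies just below 85%. A single hospital of about 35 patients can cross the line on one removal. These figures rest on the assumed f and on removal being confined to non-adherent patients.

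**What to change.** In the population definition, state that contraindication status for the primary analysis is judged on conditions present at the first successful ERCP. Apply this identically in both periods and to operated and non-operated patients. Patients whose contraindication first arises later stay in the denominator.

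A cut-off at 72 hours would not be a clean substitute. A patient who becomes unfit at 48 hours without an operation could still be excluded, while one operated on at 24 hours could not, so the exclusion would still depend partly on the outcome.

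Add two sensitivity analyses:
- (a) also exclude patients whose contraindication arose between the ERCP and 72 hours;
- (b) keep all contraindicated patients in the denominator.

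The second is feasible because these patients are already recorded in the database. The cost is one date or timing field, a little extra analysis and possibly slightly lower reported adherence. Patient care is not affected.
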